# Colorectal liver metastatic disease: efficacy of irreversible electroporation—a single-arm phase II clinical trial (COLDFIRE-2 trial)

**DOI:** 10.1186/s12885-015-1736-5

**Published:** 2015-10-24

**Keywords:** Irreversible electroporation (IRE), Liver neoplasms/secondary, Local, FDG-PET, PET-CT, Tumor ablation, Neoplasm recurrence, Colorectal liver metastases

## Abstract

**Background:**

Irreversible electroporation (IRE) is a novel image-guided tumor ablation technique that has shown promise for the ablation of lesions in proximity to vital structures such as blood vessels and bile ducts. The primary aim of the COLDFIRE-2 trial is to investigate the efficacy of IRE for unresectable, centrally located colorectal liver metastases (CRLM). Secondary outcomes are safety, technical success, and the accuracy of contrast-enhanced (ce)CT and ^18^F-FDG PET-CT in the detection of local tumor progression (LTP).

**Methods/design:**

In this single-arm, multicenter phase II clinical trial, twenty-nine patients with ^18^F-FDG PET-avid CRLM ≤ 3,5 cm will be prospectively included to undergo IRE of the respective lesion. All lesions must be unresectable and unsuitable for thermal ablation due to vicinity of vital structures. Technical success is based on ceMRI one day post-IRE. All complications related to the IRE procedure are registered. Follow-up consists of ^18^F-FDG PET-CT and 4-phase liver CT at 3-monthly intervals during the first year of follow-up. Treatment efficacy is defined as the percentage of tumors successfully eradicated 12 months after the initial IRE procedure based on clinical follow-up using both imaging modalities, tumor marker and (if available) histopathology. To determine the accuracy of ^18^F-FDG PET-CT and ceCT, both imaging modalities will be individually scored by two reviewers that are blinded for the final oncologic outcome.

**Discussion:**

To date, patients with a central CRLM unsuitable for resection or thermal ablation have no curative treatment option and are given palliative chemotherapy. For these patients, IRE may prove a life-saving treatment option. The results of the proposed trial may represent an important step towards the implementation of IRE for central liver tumors in the clinical setting.

**Trial registration:**

Trial registration number: NCT02082782.

## Background

Colorectal cancer causes each 10th death due to cancer in Western countries. About 33 % of all patients with colon cancer have liver-only metastatic disease [1]. For these patients, surgical resection is the gold standard, with 5-year survival rates up to 60 % [2, 3]. However, despite improvements of surgical techniques and current neoadjuvant chemotherapies, only 5–20 % of patients with colorectal liver metastases (CRLM) can benefit from surgery due to number, localization, or distribution of tumors [4].

In light of the limitations of surgical resection for many hepatic tumors, a number of ablative technologies for liver-directed therapy have developed during the last 20 years [5]. Of these techniques, thermal ablation using radiofrequency ablation (RFA) and microwave ablation (MWA) are most frequently used. A recent review showed a local recurrence rate of 2.8–29.7 % of RF-ablated liver lesions at 12–49 months follow-up, and 2.7–12.5 % of MW-ablated lesions at 5–19 months follow-up, with a 5-year survival rate around 30 % for both techniques [6]. Although thermal ablation has dramatically improved survival rates for patients with CRLM, factors like size and location limit its use and effectiveness. Efficacy of RFA rapidly decreases for lesions > 3 cm [7]. Also, the rate of complete tumor necrosis falls below 50 % when vessels larger than 3 mm abut the tumor as a consequence of the heat-sink effect [8]. Ablation of lesions close to vital structures like major bile ducts and vessels is associated with a substantial risk of complications due to thermal damage.

Irreversible electroporation (IRE) is a novel ablation modality that may overcome some of the limitations of current thermal ablation therapies. It is based on a pulsating current created between multiple needle electrodes placed around the target lesion which alters the existing cellular transmembrane potential. If the duration of the applied electrical pulses is below the charging time of the outer cell membrane, an interaction of the electric field with subcellular structures occurs [9]. This interaction results in permanent permeabilization of the cell membrane, which disrupts cellular homeostasis and ultimately leads to cell death. The irreversibly damaged cells are removed by the immune system [10]. Two main factors stimulate research into IRE as an ablation modality. Since the mechanism of cell death is predominantly nonthermal, connective tissue structure is preserved, so there is no damage to associated blood vessels and bile ducts [11–13]. For the same reason, treatment efficacy is not impeded by heat-sink [14]. This allows for treatment of liver tumors deemed unresectable or ineligible for other focal ablation techniques due to localization near these structures [15].

The capability of IRE to destroy CRLM in humans was recently demonstrated in the COLDFIRE-1 ablate-and-resect trial [16]. In this trial resectable CRLM were treated with IRE, followed by resection one hour later. The investigators demonstrated cell death of the ablated tumors within one hour after IRE, with intact larger vascular and ductal structures within the ablation zone. The first studies investigating hepatic IRE on clinical indication also yield promising results. A systematic review found an overall complication rate of 16 % for hepatic IRE, similar to RFA [17]. However, the tumors treated with IRE were all located near thermally sensitive structures, as opposed to the thermally ablated lesions. Complete tumor eradication was achieved in 67–100 %, and this percentage was even higher for tumors < 3 cm [17]. However, since most studies are retrospective with short-term follow-up using heterogeneous study populations and design, the value of the current evidence remains limited. Also, the optimal imaging modality for follow-up after IRE needs to be analyzed.

The primary aim of the COLDFIRE-2 trial is to investigate the efficacy of IRE for CRLM that are unsuitable for resection and thermal ablation due to the vicinity of vulnerable structures such as bile ducts, vessels and bowel. Other outcomes are safety of IRE, and the accuracy of contrast-enhanced computed tomography (ceCT) and ^18^F-fluorodeoxyglucose (FDG) positron emission tomography (PET) CT in the detection of local tumor progression (LTP).

## Methods/design

### Design

The COLDFIRE-2 trial is a phase II, multicenter, prospective single-arm trial that is organized by the VU University Medical Center in Amsterdam, the Netherlands. Patients will be recruited at three academic hospitals in the Netherlands (VU University Medical Center, Amsterdam; Academic Medical Center, Amsterdam; Leiden University Medical Center, Leiden). The study protocol has been approved by the Medical Ethical Review Board of the VU University Medical Center. The trial is investigator-sponsored, independent of industry and is registered at clinicaltrials.gov under number NCT02082782. The trial will be conducted in accordance with the Declaration of Helsinki. The inclusion and exclusion criteria for the COLDFIRE-2 trial are summarized in Table 1.

**Table 1 Tab1:** In- and exclusion criteria

Inclusion criteria	Exclusion criteria
Histologic proof of primary colorectal tumor	Ventricular cardiac arrhythmias
Radiologic proof of colorectal liver metastasis, unsuitable for resection and thermal ablation due to vicinity to vascular or ductal structures	Congestive heart failure, NYHA Class ≥ 3
^18^F FDG-PET avidity of target lesion and visible on ceCT	Active coronary artery disease
Lesion size ≤ 3.5 cm	History of epilepsy
Adequate bone marrow, liver and renal function	Any implanted stimulation device
ASA-classification 0–3	Chemotherapy <6 weeks prior to treatment

### Eligibility criteria

All patients are treated with curative intent and must have received previous chemotherapy for CRLM at some stage in their disease. Prior to inclusion, all patients will be discussed in a multidisciplinary liver tumor board consisting of a hepatogastroenterologist, hepatobiliary surgeon, medical oncologist, radiation oncologist, abdominal and interventional radiologist. Decision on treatment will be at their discretion. Patients who present with more than one metastasis can only be included if treatment with curative intent is still realistic and if all lesions can be treated during the same session or within six weeks after the IRE procedure. Thermal ablation or resection of concomitant lesions during the same session is therefore allowed and limited extrahepatic disease, defined as ≤5 nodules in the lung and/or one other metastatic site which is amenable to future definitive treatment, is not contra-indicated [18]. All participants from all participating centers will provide written informed consent.

### IRE procedure

Depending on concurrent treatment of other lesions (surgical resection or thermal ablation), patients will either be treated during an open procedure using intra-operative ultrasound (IOUS), or percutaneously using CT. Patients undergoing laparotomy will receive a thoracic epidural before surgery. For percutaneous procedures, to allow repeated and real-time visualization of both the tumor and the adjacent vessels, a catheter is placed within the common hepatic artery approaching from the right femoral artery. Technical details of this procedure have been previously described by Van Tilborg et al. [19]. All procedures will be performed under general anesthesia, induced with propofol, sufentanil, and rocuronium and maintained with propofol and remifentanil. First, the exact three-dimensional measurements of the target lesion are defined using IOUS or aortic catheter based CT. The planned electrode configuration must result in an expected geometry of the ablation zone that fully covers the tumor and a tumor-free margin of at least 5 mm in all directions [20]. Depending on the size, 2–6 needle electrodes (NanoKnife, AngioDynamics, Latham, NY) with an active working length of 20 mm are positioned in the outer border or just adjacent to the tumor under IOUS or CT guidance, aiming at an inter-electrode distance of 20 mm (±2 mm). All needles are placed parallel to each other to promote homogeneous energy delivery. After confirmation of correct distances with IOUS or with unenhanced CT using multiplanar reformatting, ten test-pulses of 1500 V/cm and 90 μs are delivered via each electrode pair, after which the delivered current is verified. The target current lies between 20–50A and voltage settings are manually adjusted in case of over- or undercurrent. Subsequently, three cycles of 30 pulses are administered to reach a total of 100 pulses per electrode pair. If more than 6 electrodes are needed for larger tumors, electrodes are repositioned to perform overlapping ablations. Similarly, for tumors with a depth larger than 20 mm, after ablation of the deepest part of the tumor a 1.5 cm pullback of the electrodes is performed to treat the superficial part. Immediately after IRE, a control aortic catheter CT or IOUS is made to evaluate technical success and to exclude early complications. The next day, ceMRI is performed to verify patency of vascular and ductal structures, as well as technical success. In case of incomplete ablation on ceMRI, the suspected residual tumor will be retreated in the following weeks. A flow diagram of the trial is shown in Fig. 1.

**Fig. 1 Fig1:**
[figure not shown]
Flow diagram of study procedure

### Imaging

Four-phase liver CT and ^18^F-FDG PET-CT will be performed before IRE, and 3, 6, 9 and 12 months after IRE. Imaging is conducted according to EANM guidelines with the same ^18^F-FDG PET-CT in each participating center (Philips Gemini TF PET-CT system, Philips Medical Systems, Cleveland, Ohio, USA) [21]. Whole body ^18^F-FDG PET (skull base to mid-thigh) starts 60 min after FDG injection, followed by a low-dose CT for attenuation correction and anatomical co-localization of ^18^F-FDG PET-findings. Next, a diagnostic 4-phase CT of the liver is performed. Scanning parameters are shown in Table 2.

**Table 2 Tab2:** Scanning parameters of 18 F-FDG PET-CT and 4-phase liver CT

	Delay (sec)	Contrast	Matrix	Pixel size (mm^2^)	Slice thickness (mm)	Current (mAs/slice)	Energy (keV)
Whole body PET		^18^F FDG (ref)	144 × 144	4 × 4	5		
Low-dose CT		-	512 × 512	1.17 × 1.17	5	30–50	100
4-phase liver CT		100 ml	512 × 512	0.68 × 0.68	4–5		
- Precontrast		Xeneti × 300				220 AEC	120
- Arterial	12					450 AEC	80
- Venous	50					220 AEC	120
- Hepatic	220					175 AEC	120

*AEC*; Automated exposure control

Treatment response is primarily based on a per-lesion analysis. The standard of reference is defined by a combination of 4-phase liver CT and ^18^F-FDG PET-CT, and, if available, histologically proven malignancy. Pathologically elevated carcinoembryonic antigen (CEA) is used when appropriate (e.g. if no other metastases are present).

Treatment response on 4-phase liver CT is assessed using the Response Evaluation Criteria In Solid Tumors (RECIST) [22]. The Positron Emission tomography Response Criteria In Solid Tumors (PERCIST) criteria are used for ^18^F-FDG PET-CT [23]. On 4-phase liver CT, LTP is defined as a growing (>20 %; longest diameter; axial plane) hypodense lesion within 1 cm of the ablation zone. On ^18^F-FDG PET-CT, focally increased FDG uptake within 1 cm of the ablation region is considered an LTP [24]. If LTP is suspected on both modalities during follow-up, the patient will be evaluated for re-treatment in our multidisciplinary liver tumor board. To establish the value of PET-CT and ceCT for the prediction of LTP the suspected area will be biopsied in the same session prior to re-treatment, although the suspicious lesion will be re-ablated regardless. In case of discrepancy between the 4-phase liver CT and ^18^F-FDG PET-CT findings, a liver MRI will be performed as problem solver. If MRI is also inconclusive, multidisciplinary deliberation will decide upon either repeat imaging 3 months later, or biopsy of the suspected recurrence. If chemotherapy is indicated during follow-up (e.g. due to new metastatic disease), the patient will remain in follow-up. The trial will end twelve months after the last IRE procedure. If no LTP or new metastatic disease has been diagnosed at this moment, regular follow-up will be resumed consisting of 6-monthly ^18^F-FDG PET-CT and 4-phase liver CT.

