After IRE, immediate ceCT shows a hypodense ablation zone that does not enhance post-contrast. A transient peripheral rim of contrast enhancement can be present, representing hyperemia [15]. In the months after ablation, the ablation zone slowly decreases in size and should not show uptake of contrast. PET scans show a dynamic response to the IRE ablation. Three days following IRE, an ^18^F-FDG-avid peripheral zone surrounding the ablated region appears. This initial increase in uptake at the periphery of the IRE region may be explained by an inflammatory response, increasing metabolic activity at the targeted region as the cellular debris is removed from the ablation site [15]. In our experience the inflammatory response can persist for several months, which renders evaluation of the ablation zone with ^18^F-FDG PET difficult. On the contrary, ablated lesions that show focal rather than rim-like uptake in the periphery are considered suspect for local recurrence. Because much is still unknown about the imaging characteristics of liver lesions treated with IRE, standardized follow-up regimens are lacking. The COLDFIRE-2 trial focuses on the typical imaging characteristics of electroporated CRLM over time. The gold standard for LTP is histologic confirmation. With biopsies taken from all suspicious lesions prior to re-treatment, the trial also assesses the accuracy of the pre-defined definition of LTP on PET-CT and ceCT.

A potentially curative treatment option for a group of patients that is currently offered chemotherapy with palliative intent is of major importance. IRE may prove a safe and valuable fortification in the armory of interventional oncologists treating patients with liver tumors. The aim of the COLDFIRE-2 trial is to contribute to the available evidence on IRE with respect to safety, efficacy, imaging characteristics and follow-up guidelines. The results of the proposed trial may represent an important step towards the implementation of IRE for central liver tumors in the clinical setting.

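### The reference standard for local tumor progression is inconsistent, and read literally it gives a negative biopsy no role

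*Protocol article*

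**What the plan says.** All references are to the protocol article.

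- **Methods/design, Imaging (reference standard):** "The standard of reference is defined by a combination of 4-phase liver CT and ^18^F-FDG PET-CT, and, if available, histologically proven malignancy". CEA is added where appropriate.
- **Same section (path to re-treatment):** "If LTP is suspected on both modalities during follow-up, the patient will be evaluated for re-treatment in our multidisciplinary liver tumor board". The purpose of the biopsy is given next: "To establish the value of PET-CT and ceCT for the prediction of LTP the suspected area will be biopsied in the same session". It precedes re-treatment, "although the suspicious lesion will be re-ablated regardless". Lesions on which CT and PET-CT disagree follow another route: MRI, then repeat imaging or biopsy.
- **Abstract, Methods/design:** 12-month efficacy is "based on clinical follow-up using both imaging modalities, tumor marker and (if available) histopathology".
- **Primary and secondary objectives:** primary efficacy is judged by RECIST and PERCIST, and histology is not mentioned. Successful repeat ablation after LTP is credited to the secondary efficacy rate.
- **Sample size calculation and statistical considerations:** sensitivity and specificity of each modality are calculated against the reference standard, and McNemar's test compares the two.
- **Discussion, Imaging follow-up:** "The gold standard for LTP is histologic confirmation", and "With biopsies taken from all suspicious lesions prior to re-treatment, the trial also assesses the accuracy of the pre-defined definition of LTP".

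**The concern.** The accuracy of CT and PET-CT is a named secondary endpoint. The only operative definition of its reference standard is made from those same two tests, plus histology when it proves malignancy. The biopsy is the one independent piece of evidence, and the definition gives it a role only when it agrees with positive imaging.

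Taken at its word, this leaves a lesion that is positive on both scans and biopsy-negative labelled as LTP. The error that the biopsy was meant to detect, a false alarm shared by both modalities, then cannot appear in the results. The primary endpoint is touched as well, because the abstract brings histopathology into the efficacy judgement and the objectives section does not.

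The case is foreseeable. The Discussion says that inflammation after IRE can last for months and complicate PET reading, and that reactive tissue and viable tumor can look alike on CT.

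**Working it through.** **1. The statements applied to one lesion** (positive on CT and PET-CT, biopsy negative):

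| Source | Status of the lesion |
|---|---|
| Imaging, reference standard, read literally | LTP |
| Primary and secondary objectives (RECIST, PERCIST) | Primary failure, on imaging |
| Abstract (histopathology, either direction) | Open; arguably not LTP |
| Imaging, purpose of the biopsy | The biopsy should be able to count against the imaging |
| Discussion (histology as gold standard) | Not LTP |

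These cannot all be applied at once.

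**2. The denominator.** The plan's sample size reproduces. With a Clopper-Pearson interval at a recurrence rate of 0.10 and x = 0.1n, n = 29 gives limits 0.0203 and 0.2691, width 0.2487. At n = 28 the width is 0.2535, so 29 is the smallest n with width at most 0.25. For 5% loss, 29/0.95 = 30.5, rounded up to 31. The point does not depend on this figure; 29 serves only as the denominator below.

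**3. Effect on accuracy (illustration).** Assumptions: 29 lesions, one per patient; k read as positive on both modalities; f of these biopsy-negative; all other lesions true negatives.

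- Specificity = TN/(TN + FP), PPV = TP/(TP + FP), TN = 29 − k.
- Literal reference: FP = 0, TP = k.
- Biopsy decides: FP = f, TP = k − f.

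| k, f | Literal: specificity; PPV | Biopsy decides: specificity (exact 95% CI); PPV |
|---|---|---|
| 3, 1 | 26/26; 3/3 | 26/27 = 0.963 (0.810–0.999); 2/3 |
| 3, 2 | 26/26; 3/3 | 26/28 = 0.929 (0.765–0.991); 1/3 |
| 6, 3 | 23/23; 6/6 | 23/26 = 0.885 (0.698–0.976); 3/6 |

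Under the literal reference, specificity is 100% in every row, whatever the biopsies show. For 26/26 the exact interval is 0.868–1. PPV is not among the measures the plan lists; it is included because it shows the effect most directly.

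**4. Effect on the primary rate.** With k = 3 and f = 1, efficacy is 26/29 = 89.7% if the lesion is a failure and 27/29 = 93.1% if it is not. The difference is 1/29 = 3.4 points.

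**The case against.** A reader might infer that under this plan a negative biopsy never overturns imaging, and that re-ablating regardless hides false positives. The documents do not support that.

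- **No section says that a negative biopsy is ignored.** That is an inference from one phrase. The abstract, the stated purpose of the biopsy and the Discussion all point the other way. This stands against the stronger reading. It does not remove the conflict, because the accuracy analysis refers to the reference standard and the Imaging section is where that is defined. The missing analysis plan does not excuse it either: such a plan could not follow all of these statements.
- **The biopsy precedes re-ablation, so its result can be tabulated.** This stands. What re-ablation removes is the untreated follow-up that could separate a true negative from a sampling miss. That is a reason to fix the classification rule in advance.
- **The path is narrower than all suspicious lesions.** It requires suspicion on both modalities, including growth on CT, so persistent PET inflammation alone does not trigger it. This stands, and how often the case would occur is unknown.
- **Accuracy comes from a blinded re-read.** Under Data collection and handling, readers are blinded to the other modality and to the final outcome. A lesion suspected in clinic is therefore not automatically scored positive by both. This stands, but it does not cure the label. If a blinded reader rightly calls the biopsy-negative lesion benign, the literal reference counts a false negative: with k = 3 and f = 1, sensitivity is 2/3 instead of 2/2.
- **The objectives section already largely settles primary status,** since it judges by imaging and puts repeat ablation in the secondary rate. This stands. Only the abstract's mention of histopathology leaves room for doubt.

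**Conclusion.** The concern holds as an inconsistency in the reference standard. Its only operative definition, read literally, biases specificity and PPV upward for lesions suspected on both modalities. It does not hold as a claim that the plan discards negative biopsies or that re-ablation conceals them.

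In the illustration, one negative biopsy among three lowers specificity from 100% to 96.3% and PPV from 3/3 to 2/3. These counts are assumed, and they take every other lesion to be a true negative and both blinded reads to be positive. A false positive shared by both modalities is a concordant pair, so McNemar's comparison would not change; the bias is in the absolute accuracy of each test.

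For the primary rate, the ambiguity is worth 3.4 points per lesion. That is small beside the planned interval width of 0.249, and the objectives section mostly resolves it. The point should be corrected, but it does not threaten the main conclusion of the trial.

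**What to change.** Make the abstract, the Imaging section, the objectives section and the Discussion agree, and fix the rules before the 12-month data are read.

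1. **Accuracy analysis.** Where a pre-retreatment biopsy gives a diagnostic result, positive or negative, use it as the reference for that lesion. Use composite follow-up for lesions that were not biopsied or whose sample was non-diagnostic. Add a sensitivity analysis that keeps the composite imaging label for biopsy-negative lesions, to cover sampling misses. Report accuracy against histology separately for biopsied lesions.
2. **Primary rate.** State what the objectives section already implies: a target re-ablated for suspected LTP is a primary failure whatever the biopsy shows. Add a sensitivity analysis that reclassifies biopsy-negative targets as free of LTP.
3. **Scope of biopsy.** Reconcile the Discussion, which speaks of all suspicious lesions, with the Imaging section, which describes the biopsy and re-ablation path for lesions suspected on both modalities.

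The cost is wording and two sensitivity analyses on biopsies that are already planned. The drawbacks are that a sampling miss would count as an imaging false positive in the main accuracy analysis, and that biopsied and unbiopsied lesions would have different references. The sensitivity analysis shows how much the first matters, and the separate report for biopsied lesions makes the second visible. Clinical management is unchanged.
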